### Sample size calculation

The power analysis to determine sample size of the study was based on data from the Synbiose 1 trial (i.e., combination treatment with belimumab and rituximab) and the ALMS trial (i.e., standard of care with mycophenolate and steroids) [32, 38]. To show a significant reduction in treatment failure, we assumed a treatment failure rate during the study period of 104 weeks of 54% in the standard of care group (in accordance with ALMS study results) compared to 23% in the intervention group (in accordance with the Synbiose 1 study results). We calculated that in order to demonstrate a hazard ratio of 2.97 with at least 80% power, using an alpha error confidence level of 5% and beta probability of 0.20, the study would require a total of 70 patients to be randomized with 35 patients in each group.

### Statistical analysis

The statistical analysis will primarily be performed on the intention-to-treat population. For non-biased immunological endpoints, a per-protocol analysis will be done to assess the pathophysiological effects of adding belimumab and rituximab onto standard of care. The observed rates of treatment failure will be displayed in survival curves and the difference between treatment groups will be assessed using a log-rank test.

Differences in baseline characteristics, immunological endpoints, and clinical response will be explored. The absolute and percentage reduction of autoantibody titers, memory B cells, and NET formation will be analyzed as continuous variables using the non-parametric Mann-Whitney *U* test to compare treatment groups. Clinical disease activity categorized by the aforementioned response criteria will be analyzed using the chi-square test for dichotomized variables. Dosages of immunosuppressants will be analyzed as continuous variables using Mann-Whitney *U* because of the limited number of patients. Missing data will be imputed as that subject’s previously observed value. Patients that have crossed over from the control group to the intervention group will be considered as having met the primary endpoint of treatment failure and will re-enter the study as a new subject. As such, they will be included in the intention-to-treat analysis. Also, they will serve as their own controls in an additional post hoc analysis.

Safety, toxicity, and adverse events will be documented, and the events considered to be at least possibly related to the study treatment will be summarized by severity and treatment group. Infectious AE’s will be presented to an independent infectious disease specialist for evaluation of severity and relation to study participation.

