### Study population

The study will include adult SLE patients with severe disease with major organ involvement, including LN. In brief, patients are above 18 years of age and have a clinical diagnosis of SLE according to the Systemic Lupus International Collaborating Clinics (SLICC) criteria. Severe disease is defined as either an SLE disease activity index (SLEDAI) ≥ 12, new or progressive activity in major organ systems, or otherwise high disease activity despite conventional immunosuppressive treatment, which requires remission induction therapy. Detailed in- and exclusion criteria are summarized in Table 1.

**Table 1 Tab1:** Entry criteria. In- and exclusion criteria of the Synbiose 2 study

Inclusion criteria	Exclusion criteria

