
### Randomization

Seventy patients will be randomized 1:1 to one of two treatment strategies by computer-generated allocation in blocks, to either standard of care, consisting of corticosteroids plus mycophenolate as induction and maintenance therapy, or the intervention group where induction therapy consists of standard of care with the addition of belimumab and rituximab, and maintenance therapy of low-dose prednisolone and belimumab. Enrolment and randomization will be performed by the patient-treating physician researcher or primary investigator of the study center and are done as soon as possible after screening and obtaining informed consent, ideally before initiation of remission induction treatment, with a maximum of 4 weeks thereafter.

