### Study endpoints

The primary clinical endpoint is the proportion of patients with treatment failure during the trial period, defined as either death, development of end-stage renal disease, major renal or extrarenal flare, sustained doubling of serum creatinine, clinical or renal non-response, requiring induction therapy or plasmapheresis, requiring a dose reduction or discontinuation of mycophenolate—other than established by protocol—for more than 14 or 7 days respectively, discontinuation of belimumab for more than three consecutive doses, inability to complete two rituximab administrations, withdrawal for any reason, or loss to follow-up.

Secondary clinical endpoints will be evaluated at 28 and 104 weeks. Clinical response is defined as a reduction in SLEDAI of ≥ 4 points and no worsening of Physician Global Assessment (PGA) score of > 0.3 points on a scale of 0–3. Other secondary endpoints are clinical remission (defined as meeting the criteria of clinical response and additionally achieving to taper steroids to ≤ 5 mg/day), renal response (complete renal response being < 0,75gr proteinuria per 24 h and a serum creatinine within 125% of baseline), low-level disease activity (SLEDAI ≤ 4 with no activity in major organ systems, hemolytic anemia or gastrointestinal activity and no new disease, PGA ≤ 1 and ≤ 7.5mg prednisolone equivalent), and disease control (SLEDAI ≤ 2 with ≤ 5mg steroids per day) [36]. Patient-reported outcome measure includes the SF-36 Quality of Life questionnaire [37]. Other clinical secondary endpoints are feasibility and safety of combination treatment by monitoring the occurrence of adverse events, with special attention to infections.

The main immunological endpoint is reduction of anti-dsDNA and other disease-specific autoantibodies at 28 weeks, which is also assessed at 104 weeks. Secondary immunological endpoints are reduction of relevant autoantibodies, sustained B cell depletion, and regression of immune complex-mediated excessive NET production at 28 and 104 weeks.

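### The stated primary log-rank test is not stratified by lupus nephritis, which is likely prognostic and not stated to be balanced at randomisation; stratifying would cheaply protect against chance imbalance.

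*Protocol article*

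**What the plan says.** The Statistical analysis section displays treatment failure as survival curves and states that "the difference between treatment groups will be assessed using a log-rank test". It names no stratum or covariate for this test; baseline differences are only to be explored.

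The Randomization section states: "Seventy patients will be randomized 1:1 to one of two treatment strategies by computer-generated allocation in blocks". No stratification factor is given.

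The Study population section reads "The study will include adult SLE patients with severe disease with major organ involvement, including LN", and Table 1 lists nephritis as one of several alternative ways to qualify as severe. The trial therefore holds patients with and without nephritis.

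Under Study endpoints, the failure composite includes "development of end-stage renal disease, major renal or extrarenal flare, sustained doubling of serum creatinine, clinical or renal non-response". It also includes components with no renal content, among them "inability to complete two rituximab administrations, withdrawal for any reason, or loss to follow-up".

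Table 2 schedules a 24-hour urine analysis at screening, and a kidney biopsy there when renal involvement is suspected. Nephritis status can therefore be known before treatment is compared.

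**The concern.** Patients with nephritis have routes to failure that other patients lack or rarely meet: failure to respond renally, renal flare, doubling of creatinine and end-stage renal disease. If these raise their total failure rate, an arm that receives more nephritis patients by chance will look worse for a reason unrelated to treatment. An unstratified test does not correct for this.

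The trial is small (35 per arm, about 27 expected events), so such imbalances are not rare. If one shows in the baseline table of an open-label trial, an adjustment added at that stage will look data-driven. Only an adjustment written down beforehand avoids that. When a factor is strongly prognostic, leaving it out of the test can also cost some power.

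**Working it through.** **Inputs from the article.** Failure by 104 weeks of 54% (control) and 23% (intervention); hazard ratio 2.97; alpha 5% (taken as two-sided, which reproduces the stated size); 80% power; 35 per arm.

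**The plan's own figure.**
- Hazard ratio: ln(1 - 0.54) / ln(1 - 0.23) = 2.97.
- Events (Schoenfeld): 4 × (1.960 + 0.842)² / (ln 2.97)² = 26.5, rounded up to 27.
- Patients: mean failure rate (0.54 + 0.23)/2 = 0.385, and 27 / 0.385 = 70.1.
- With 70 patients: 70 × 0.385 = 26.95 events, giving 80.7% power.

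The planned 70 reproduces from an unadjusted two-group log-rank calculation, so sample size and stated test agree.

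**Assumptions the article does not supply.** Nephritis share 30%, 50% or 70%; nephritis hazard ratio 1, 1.5, 2, 3 or 0.5; unstratified permuted blocks of 4; exponential failure times; 70 independent patients. Overall failure was held at 54% and 23% for power, and at 54% in both arms for type I error. Each scenario used 40,000 simulated trials (simulation error about 0.2 points for power and 0.3 for type I error among imbalanced trials).

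**Chance of imbalance.** A difference in nephritis share of at least 15 points between arms occurred in 16-19% of simulated trials, and of at least 20 points in 7-10%. As a check at a 50% share, two independent Binomial(35, 0.5) counts differ by 6 or more (6/35 = 17 points; 5/35 = 14 falls short) with probability 18.8%. Smaller repeat simulations at 50% gave 18-20%.

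**What such an imbalance does to the failure rates.** Take a 50% share and control failure of 54%, and let y be the proportion of non-nephritis controls without failure.
- Nephritis hazard ratio 2: y² + y = 2 × 0.46 = 0.92, so y = 0.582. Failure is 66% with nephritis and 42% without. A 15-point imbalance shifts the failure difference by 0.15 × 24 = about 4 points.
- Nephritis hazard ratio 3: y³ + y = 0.92, so y = 0.648. Failure is 73% and 35%, and the shift is 0.15 × 38 = about 6 points.

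The planned difference is 54 - 23 = 31 points.

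**Plain against stratified log-rank** (ranges over nephritis share 30-70%):

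| Nephritis hazard ratio | Power, plain | Power, stratified | Type I error if imbalance ≥ 15 points, plain | Same, stratified |
|---|---|---|---|---|
| 1 | 78.2-78.3% | 77.3-77.5% | 4.5-4.9% | 4.4-4.9% |
| 1.5 | 78.4-78.9% | 78.3-78.6% | 5.4-5.8% | 5.1-5.5% |
| 2 | 78.2-78.5% | 79.0-79.5% | 6.3-6.8% | 4.8-5.3% |
| 0.5 | 78.3-78.6% | 79.2-79.7% | 6.4-6.8% | 5.0-5.3% |
| 3 | 78.6-79.0% | 81.1-83.1% | 7.6-9.2% | 5.0-5.6% |

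Over all trials, imbalanced or not, type I error was 4.9-5.3% for both tests. The power gain at hazard ratio 3 is 2 to 4 points here and up to about 5 in the smaller repeat runs.

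**The case against.** The strongest reply is that nothing here is an error. A plain log-rank test is valid under randomisation, its overall type I error is 5%, and the sample size was derived for it. All of that stands.

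The article is also a condensed account. Stratification factors and covariates may be set in the full protocol or the SAP, neither of which is shown. A reader might infer that randomisation was certainly unstratified, or that the trial as a whole ignores nephritis. The article supports only that it states neither a stratification factor nor an adjustment.

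A reader might also take nephritis to be prognostic by construction. That does not follow. The composite includes many components unrelated to the kidney, such as drug interruption, withdrawal and loss to follow-up. Patients without nephritis are also severely ill and have their own routes to failure. The article gives neither the nephritis share nor failure by nephritis status, so direction and size are unknown. Likely prognostic is as far as one can go.

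Finally, a reader might conclude that the plan forfeits power. With both planned failure rates held, plain power stays at 78-79% for nephritis hazard ratios from 1 to 3. A steeper loss appears only if the treatment hazard ratio is fixed at 2.97 within strata: at a 50% share and a nephritis hazard ratio of 4, power is 71% plain against 79% stratified. In that setting intervention failure rises from the planned 23% to 25.4%, so part of the fall is a smaller overall effect. A ratio of 4 also means control failure of about 77% with nephritis and 31% without, a gap that nothing in the article supports.

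The chance of an uncorrected imbalance, and the low price of guarding against it, survive these points.

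**Conclusion.** The point holds as a recommendation on robustness, with a modest and conditional effect on efficiency. It identifies neither an invalid test nor an inconsistent sample size. About one trial in six to one in five of this size would carry a nephritis imbalance of at least 15 points. The stated test would then be somewhat miscalibrated if nephritis is prognostic: about 6-7% type I error at a nephritis hazard ratio of 2 and 8-9% at 3, against about 5-6% when stratified. The average power change from stratifying runs from about -1 point (not prognostic), through 0 to +1 (hazard ratio 1.5 to 2), to +2 to +5 (hazard ratio 3). These sizes rest on an assumed nephritis share, prognostic strength, block size and failure-time distribution. The article fixes none of them.

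**What to change.** First check whether the full protocol or SAP already stratifies the randomisation or the primary test by nephritis. If the primary test is already stratified there, only the published description needs aligning.

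Otherwise, before any comparative data are examined (the Trial status section expects completion in September 2025), prespecify:
- the primary test as a log-rank test stratified by lupus nephritis at screening (yes/no), with that status defined from the screening assessments;
- the hazard ratio from a Cox model stratified in the same way;
- the unstratified log-rank test as a sensitivity analysis.

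This takes about one sentence in the analysis section and needs no further patients or data. The price is about 1 point of power if nephritis turns out not to be prognostic.

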• ≥ 18 years of age • Having a clinical diagnosis of SLE according to the SLICC criteria 2012 • Severe, active SLE defined as one or more of the following: ◦ SLEDAI ≥ 12 ◦ New or worse SLE-related activity in major organs, i.e., CNS-SLE (includes NPSLE), vasculitis, nephritis, pericarditis and/or myocarditis, myositis, thrombocytopenia (< 60 × 10^9^/L), hemolytic anemia (Hgb < 4.4mmol/L = 7.0 g/dL) ◦ High disease activity that requires or warrants induction treatment by switching to or increasing dosage of oral mycophenolate • New, persisting or progressive disease activity despite the use of conventional maintenance immunosuppressive treatment (e.g., mycophenolate or azathioprine) • Confirmed positive SLE-specific autoantibodies defined as one or more of the following: ◦ ANA titer ≥ 1:80 ◦ Either 2 positive test results from independent time points within the study screening period, or one positive historical test result and 1 positive result during the screening period ◦ Anti-dsDNA serum antibody ≥ 30 IU/mL ◦ Either 2 positive test results from independent time points within the study screening period, or one positive historical test result and 1 positive result during the screening period	• Female patients who arepregnant or breastfeeding • Significant hypogammaglobulinemia (IgG < 4.0 g/L) or IgA deficiency (IgA < 0.1 g/L) • Immunization with a live vaccine within 1 month preceding day 0 • Active infection, defined as one or more of the following: ◦ Hospitalization for treatment of infection within 60 days preceding day 0 ◦ Use of parenteral antimicrobial agents within 60 days preceding day 0 ◦ Serological evidence of viral hepatitis defined as: patients positive for HbsAg or HbcAb, or hepatitis C antibody positivity, not treated with antiviral medication • Having a historically positive HIV test or test positive at screening • Having a history of a primary immunodeficiency • Having a neutrophil count of < 1.5 × 10^9^/L • Having a significant infection history that in the opinion of the investigator makes the candidate unsuitable for the study • Having a history of an anaphylactic reaction to parenteral administration of contrast agents, human or murine proteins or monoclonal antibodies • Having any other clinically significant abnormal laboratory value that in the opinion of the investigator makes the candidate unsuitable for the study • Drug or alcohol abuse or dependence within 1 year preceding day 0 • Having an active malignant neoplasm or one in the last 5 years, except basal cell or squamous cell carcinoma of the skin treated with local resection only, or carcinoma in situ of the uterine cervix treated locally and with no evidence of metastatic disease for 3 years • Having evidence of serious suicide risk, including suicidal behavior in the last 6 months and/or any suicidal ideation in the last 2 months

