**Assessments**																						
SLEDAI/PGA	x		x	x	x	x	x	x	x	x	x		x	x	x	x	x	x	x	x	x	
SLICC damage score	x														x						x	
QoL questionnaire			x					x			x				x				x		x	
Treatment failure																					x	
Clinical and renal response											x										x	
Autoantibody reduction											x										x	
B cell depletion											x										x	
NET assay			x								x										x	

*S* screening, *B* baseline, *QoL* SF-36 quality of life questionnaire, *FU* follow-up, *SBLA* standard blood laboratory analysis, *Ig* immunoglobulins, *NET* neutrophil extracellular traps

^a^Baseline may be left out if planned within two weeks of screening. ^b^Kidney biopsy only in case of suspected renal involvement

Upon severe flares of SLE disease activity, alternative treatment options will be considered, which can result in the withdrawal of the subject from the study. Patients randomized to the standard-of-care treatment group can cross over to the intervention group in the case of either a severe flare or insufficient treatment response requiring a switch in medication. They will then be considered to have met the primary endpoint of treatment failure, will re-enter the study if they fulfill the inclusion criteria, and receive the complete study treatment of the intervention group as described above.

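### The SLEDAI-based secondary responses are compared by an unadjusted chi-square test although a SLEDAI score from before randomised treatment is scheduled for every patient; the test is valid, but gives up some precision and protection against chance imbalance

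*Protocol article*

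**What the plan says.** Protocol article, Statistical analysis: "Clinical disease activity categorized by the aforementioned response criteria will be analyzed using the chi-square test for dichotomized variables". No covariate, stratum or model is named. On baseline the section says only that "Differences in baseline characteristics, immunological endpoints, and clinical response will be explored"; no adjustment is tied to that exploration.

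Study endpoints: "Clinical response is defined as a reduction in SLEDAI of ≥ 4 points", together with a condition on the physician global assessment. Clinical remission adds a steroid limit to clinical response. Low-level disease activity and disease control instead require a SLEDAI of at most 4 or at most 2, again with steroid limits. All are evaluated at weeks 28 and 104.

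Table 2 schedules SLEDAI at screening and at the baseline visit. Its footnote reads "Baseline may be left out if planned within two weeks of screening", so a patient without a separate baseline visit still has a screening score.

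Table 1: "Severe, active SLE defined as one or more of the following". A SLEDAI of 12 or more is only one of the routes listed, so lower scores can enter. Under Randomization, allocation is 1:1 "by computer-generated allocation in blocks", with no stratification by disease activity stated. The sample size section gives 35 patients per arm.

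**The concern.** Each of the four responses depends by definition on SLEDAI, either as a fall from the starting score or as a level to be reached. The starting score is therefore a natural predictor, it is already collected, and the planned 2×2 test ignores it. Two things follow if it is prognostic. First, the comparison is less precise than the data allow. Second, a chance difference in starting SLEDAI between two arms of 35 passes directly into the response rates, and the design as described does nothing to limit such a difference. Settling the adjustment in advance matters more in an open-label trial, where a covariate added after baseline differences have been explored would look chosen to suit the result.

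**Working it through.** **1. The plan's own figure.** The only stated calculation is for the primary endpoint, with failure rates of 54% and 23%. Hazard ratio = ln(0.46)/ln(0.77) = 2.97. Schoenfeld events, two-sided 5%, 80% power: 4 × (1.960 + 0.842)² / (ln 2.97)² = 26.5, rounded up to 27. Mean failure rate = (0.54 + 0.23)/2 = 0.385, and 27/0.385 = 70.1. The stated 70 is reproduced. It says nothing about the secondary responses, for which no power is claimed.

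**2. Inputs for the secondary comparison.** From the article: 35 per arm. Assumed: two-sided 5%; response rates of 46% and 77%, the complements of the failure rates, since no response rates are given; and a latent correlation r between starting SLEDAI and outcome, varied because the article gives none.

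**3. Power by simulation.** 6,000 trials per row, latent-normal outcome, Pearson chi-square against the likelihood-ratio test of arm in a logistic model with baseline:

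| r | Chi-square | Adjusted | Raw gain | Less 1.0 point for test size |
|---|---|---|---|---|
| 0.3 | 77.8% | 80.0% | 2.2 | 1.2 |
| 0.5 | 77.6% | 84.6% | 7.0 | 6.0 |
| 0.7 | 77.9% | 91.0% | 13.1 | 12.1 |

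The 1.0 point is the excess seen at r = 0, where adjustment cannot help. It reflects a type I error of about 5.5% for the likelihood-ratio test against about 4.5% for chi-square. In a separate run with the adjusted test held to exactly 5%, its power was 78%, 84% and 90%, against 78%, 77% and 77% for chi-square.

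**4. The same comparison with the test recommended below.** Standardised risk difference, 4,000 trials per row:

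| r | Chi-square | Adjusted | SD ratio, adjusted/unadjusted |
|---|---|---|---|
| 0 | 77.7% | 78.9% | 1.01 |
| 0.2 | 77.9% | 79.6% | 0.995 |
| 0.4 | 76.7% | 81.6% | 0.956 |
| 0.6 | 77.3% | 87.6% | 0.893 |

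Cross-check by formula, with effective n per arm = 35/(1 − R²). Unadjusted power is 77.2%. R² = 0.10 gives 35/0.90 = 38.9 per arm and 81.5%; R² = 0.20 gives 35/0.80 = 43.8 per arm and 85.9%. The SD ratios at r = 0.4 and 0.6 correspond to R² = 1 − 0.956² = 0.09 and 1 − 0.893² = 0.20, so formula and simulation agree to within about 2 points.

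**5. Chance imbalance.** The standard error of the difference in mean starting SLEDAI, in SD units, is √(2/35) = 0.239. A gap of at least 0.4 SD is 0.4/0.239 = 1.67 standard errors, with two-sided probability of about 9%; the simulations gave 8% to 10%. With 55% response in both arms, the chi-square test rejects in 4.4% to 5.0% of all trials. Within the imbalanced trials it rejects in about 7% at r = 0.4 and 15% at r = 0.6, against about 5% and 6% for the adjusted test. Each conditional rate rests on roughly 400 trials, so it is good to about 2 points either way.

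**6. Sparse responses.** With an assumed 10% response in both arms, the likelihood-ratio test has a type I error of about 7% (chi-square 5% to 6%). At 5% response it is about 9% (chi-square 3% to 4%), with an empty arm or near-separation in about 30% of trials. The test of the standardised risk difference stays at about 4% to 7% for responses of 5% to 10%.

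**The case against.** The strongest reply is that nothing here is an error. An unadjusted chi-square test is valid in a randomised trial, and the null runs confirm it. The endpoints are secondary and carry no power claim, baseline and response differences are described as exploratory, and an unseen analysis plan may add a covariate. The first part stands: a reader might infer that the planned test is biased or inflates false positives, and over all randomisations it does not. The last part stands only partly, because the article states the test rather than leaving it open.

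The second reply is that the size is assumed. This stands. The 46% and 77% are complements of a composite failure endpoint that also counts withdrawal and drug changes over 104 weeks. Three of the four responses also need a steroid limit, which may weaken the link with SLEDAI. At r of 0.3 or below almost nothing is gained.

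A reader might also infer that one imbalance would push the change-based and level-based responses in opposite directions and make them contradict each other. The definitions make this conceivable, but the article gives no data on it, and for patients entering at 12 or above a 4-point fall is not limited by lack of room. No such effect was quantified.

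Nor is the score safely called pre-treatment. Randomisation may follow the start of induction by up to 4 weeks, so a score may be taken on induction therapy. It is still a legitimate covariate if it precedes randomisation.

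Finally, the article lets control patients who cross over re-enter as additional subjects in the intention-to-treat analysis. A re-entry score is measured after the original randomisation and after failure, so it is no baseline covariate for the randomised comparison. The simulations assume 35 independent patients per arm and do not cover this.

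**Conclusion.** The point holds as one of efficiency and of protection against chance imbalance, for the four SLEDAI-based responses at weeks 28 and 104. It does not extend to renal response, which is not defined by SLEDAI, or to the primary analysis. Under the assumed rates of 46% and 77%, the gain in power is about 0 to 2 points at a latent correlation of 0.3 or below, 5 to 6 at 0.5 and 12 to 13 at 0.7. In roughly one trial in ten the arms would differ by 0.4 SD or more at baseline, and there the unadjusted result can mislead if SLEDAI is moderately or strongly prognostic. Because the prognostic strength is unknown, the benefit may be close to nothing. The change is worth making because it is cheap and uses data already collected, not because the present test is wrong.

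**What to change.** Keep the response definitions. For each SLEDAI-based response at weeks 28 and 104, prespecify as the main analysis:

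- a logistic model with arm and the last SLEDAI before randomisation, entered as a continuous covariate;
- from it, the baseline-standardised risk difference with 95% CI and the test of that difference, not the likelihood-ratio test;
- each patient in the originally randomised arm with the pre-randomisation score, never a re-entry score after crossover;
- the chi-square test, or an exact test, as sensitivity analysis, and as the fallback when an arm has too few responders to fit the model.

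Name the visit that supplies the score. Table 2 places the allocation column before the baseline visit, so on that layout the screening score is the one sure to precede randomisation.

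The cost is a few sentences in the analysis section and a few lines of code, with no new data. The downside is small: an analysis that is somewhat harder to present and depends on a model, with little return if SLEDAI is only weakly prognostic.

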### Study treatments

All patients will be given standard of care consisting of 3 pulses of 500 mg (< 60 kg) or 1000mg (> 60 kg) of intravenous methylprednisolone. This will be followed by tapered oral prednisolone at a starting dose of 60mg daily together with mycophenolate at a starting dose of 500mg twice daily and increased weekly, titrated to achieve a target AUC of 60-90mg*h/L, with a maximum dose of 4000mg per day. In cases where therapeutic drug monitoring (TDM) is not possible, mycophenolate dose will be titrated against leukocyte counts and tolerability of the patient. Patients randomized to the intervention group will receive standard of care combined with self-administered subcutaneous belimumab 200mg weekly, and two doses of 1000-mg intravenous rituximab 4 and 6 weeks after belimumab initiation. One hundred-milligram intravenous methylprednisolone, 2-mg intravenous clemastine, and 1000-mg oral acetaminophen will be administered prior to rituximab infusions.

In both treatment groups, oral prednisolone will be tapered to 7.5mg before week 28 and to 5mg before week 52 and will be continued at a low dose for the remaining study period. Dose reduction to zero can be personalized to the tolerance of the patient, judged by the treating physician. In the control group, mycophenolate will be reduced by 50% at week 28 and continued for the remainder of the study period. In the intervention group, mycophenolate dose will be reduced by 50% at week 16 and discontinued at week 28. Belimumab will be continued throughout the entire study period. Consequently, after week 28, patients will enter the maintenance phase where they will receive either prednisolone and mycophenolate (control group) or prednisolone and belimumab (intervention group) (Fig. 1). Patients will be monitored closely during the study, with laboratory evaluation and study visits every 2 weeks during the first 8 weeks after inclusion, and increasingly longer intervals during the remainder of the study, up to 2 months eventually. An overview of study visits and assessments per visit is summarized in Table 2.

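### Carrying the last value forward for all missing data can make one patient a primary failure and an imputed week-104 responder, and cannot show lasting B-cell depletion

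*Protocol article*

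**What the plan says.** All references are to the protocol article.

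- **Missing data (Statistical analysis).** "Missing data will be imputed as that subject’s previously observed value". The sentence is not limited to any endpoint, visit or cause. The intention-to-treat population is the main one, with a per-protocol analysis added for immunological endpoints.
- **Primary endpoint (Study endpoints).** Treatment failure includes death, "withdrawal for any reason, or loss to follow-up", and also "clinical or renal non-response, requiring induction therapy or plasmapheresis".
- **Secondary clinical endpoints (Study endpoints).** "Secondary clinical endpoints will be evaluated at 28 and 104 weeks". The responder rule is: "Clinical response is defined as a reduction in SLEDAI of ≥ 4 points and no worsening of Physician Global Assessment (PGA) score", with a PGA margin of 0.3 points. It does not require the patient to be alive, still followed or free of treatment failure.
- **Immunological endpoints.** These include autoantibody reduction, "sustained B cell depletion, and regression of immune complex-mediated excessive NET production at 28 and 104 weeks". In the analysis, "The absolute and percentage reduction of autoantibody titers, memory B cells, and NET formation will be analyzed as continuous variables".
- **Follow-up (Ethical considerations and dissemination).** Patients who stop study medication keep attending the planned visits unless they withdraw consent.

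**The concern.** The primary analysis counts leaving the trial as a bad outcome. The secondary analysis of the same patient assumes that the last recorded state persisted to week 104. Non-response is itself a component of treatment failure, so the two analyses can read one patient in opposite ways.

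For the biological endpoints, the week-104 question is whether an effect induced early has lasted. A value recorded long before and copied forward assumes the answer. At stake is how far the week-104 response, depletion, autoantibody and NET comparisons can be believed. The primary comparison is not in question.

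**Working it through.** **1. The plan's own figure.** Sample size calculation gives failure rates of 54% and 23%, a hazard ratio of 2.97 and 70 patients. Check: ln(0.46)/ln(0.77) = 2.97. Schoenfeld's formula (two-sided 5% assumed, 80% power) gives (1.960 + 0.842)² / (0.25 × (ln 2.97)²) = 26.5, so 27 events. The mean failure probability is (0.54 + 0.23)/2 = 0.385, and 27/0.385 = 70.1. The figure reproduces. It contains no drop-out rate, and none appears elsewhere in the article.

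**2. One patient, two scores.** Take a patient whose SLEDAI has fallen by at least 4 points at week 28, with PGA no worse, and who is lost at week 40.
- Primary endpoint: failure, through loss to follow-up.
- Week-104 clinical response: the week-28 value is copied forward and meets the definition, so responder.

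The same happens after death or withdrawal of consent.

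**3. How far values are carried (Table 2), for the week-40 leaver.**

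| Measure | Last value before week 40 | Weeks carried to 104 |
|---|---|---|
| SLEDAI/PGA | week 28 (not done at week 36) | 104 − 28 = 76 |
| B-cell immunophenotyping | week 28 (not done at week 36) | 76 |
| NET assay | week 28 (done only at baseline, 28 and 104) | 76 |
| Autoantibodies | week 36 | 104 − 36 = 68 |

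A patient without a week-28 NET value would carry the baseline value.

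**4. Are the carried values stable?** Study treatments places "two doses of 1000-mg intravenous rituximab 4 and 6 weeks after belimumab initiation", long before week 104. The Introduction says that long-term belimumab restrained full B-cell repopulation, which implies some return. It also cites a cohort with rising anti-dsDNA after rituximab. Against this, it reports long-lasting autoantibody reduction under the combination, and the Discussion describes an early surge of circulating memory B cells after belimumab. A carried value could therefore flatter the intervention or count against it.

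**5. Illustration for clinical response; the shares are assumptions.** Let f be the share of failures with no week-104 data, and q the share of those whose last value meets the response definition. Double-scored patients per arm = 35 × failure rate × f × q. Expected failures are 35 × 0.54 = 18.9 (control) and 35 × 0.23 = 8.05 (intervention).

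| f, q (same in both arms) | Control | Intervention |
|---|---|---|
| 0.25, 0.25 | 1.2 | 0.5 |
| 0.50, 0.50 | 4.7 | 2.0 |
| 0.75, 0.75 | 10.6 | 4.5 |

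Assume further that all non-failures respond and failures do not: 46% vs 77%, a difference of 31 points. At f = q = 0.5, carry-forward adds 54 × 0.25 = 13.5 points to control and 23 × 0.25 = 5.75 to intervention. The difference becomes 31 − (13.5 − 5.75) = 23.25 points.

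If q differs by arm, the result can reverse. With f = 0.5, q = 0.25 in control and q = 0.75 in intervention, the additions are 54 × 0.125 = 6.75 and 23 × 0.375 = 8.6 points, and the difference becomes 31 − 6.75 + 8.6 = 32.9 points. Direction depends on quantities that the article does not give.

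**The case against.** The strongest reply is that little will be missing. Patients off study drug stay in follow-up, the primary endpoint already handles drop-out, the main immunological endpoint is at week 28, and a per-protocol immunological analysis is planned. All of this stands and limits the reach. It does not cover death, withdrawal of consent or loss, and the main analysis remains intention-to-treat.

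It is also fair that failing and responding can both be true. A patient may fail through a mycophenolate dose change and have a genuinely observed response at week 104. The fault concerns imputed values only. Sensitivity analyses may sit in the analysis plan, so their absence is not criticised; the main rule is stated here.

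A reader might infer more than the documents support:

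- **About 13% of an arm double-scored.** In the Synbiose 1 figures in the Introduction, 67% responded and 80% of those stayed on belimumab, so 0.67 × 0.20 = 13.4%, or 4.7 of 35. But that 20% did not continue a drug; they are not reported to have left follow-up.
- **54% vs 23% of records affected.** These are failure rates. Flare, non-response or a dose change does not make data missing.
- **Crossover inflates control response.** Control patients cross over for severe flare or insufficient response, so their last value mostly shows active disease and agrees with the primary score.
- **An early nadir always favours the intervention.** Step 4 shows that the direction is open.
- **Confidence intervals too narrow.** The article names tests for these endpoints, not intervals.

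**Conclusion.** The point holds for the secondary endpoints, chiefly at week 104. Followed as written, the rule can score one patient as a primary failure and a week-104 responder. It can also fill a B-cell or NET result with a value 76 weeks old, which is no evidence of durability.

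The size is unknown because no drop-out rate is given. The illustrated range of 0.5 to 10.6 patients per arm rests wholly on assumed f and q, and continued follow-up makes the upper end less likely. Clinical response differences may be diluted, and biological bias may go either way. Endpoints that require a low steroid dose (remission, low disease activity, disease control) are less exposed, since early leavers tend to carry a higher dose. The change should be made, but it does not threaten the primary analysis.

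**What to change.** Replace the single rule with rules by endpoint type.

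- **Binary endpoints** (clinical response, renal response, remission, low disease activity, disease control): where the week-28 or week-104 value is missing because of death, withdrawal, loss to follow-up or crossover, score non-response. For crossover this applies to the control-arm record. Use observed values for everyone still followed, including those off study drug.
- **Autoantibodies, B cells, SF-36 and steroid dose:** use multiple imputation, or a mixed model limited to a few key visits with a simple covariance structure. An unstructured model over all 18 post-baseline autoantibody visits would need 18 × 19/2 = 171 covariance parameters, which is not workable with 70 patients.
- **NETs:** use observed values or multiple imputation, since there are only three time points.
- **Carry-forward:** keep it only as a sensitivity analysis.

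The cost is revised wording, a little more programming and response rates that may look slightly lower. No visits need to be added. The change should be fixed before outcome data are analysed.
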